## 7.4 Rash

7.4.1 Grade 2

Antihistamines, topical corticosteroids, or a brief course of systemic corticosteroids, at the discretion of the site investigator, may be prescribed and subjects may continue RAL. The subject should be advised to contact the physician immediately if there is any worsening of the rash, or if systemic signs or symptoms develop that could be compatible with a hypersensitivity reaction (HSR).

If the rash is considered to be most likely due to concomitant illness or drug, standard management, including discontinuation of the likely causative agent, should be undertaken. If no other causative factor is found after clinical evaluation, the subject should be treated symptomatically until the rash resolves.

7.4.2 Grade 3

If the rash is thought to be related to RAL, subjects must discontinue their ARV regimen and the core team must be consulted.

7.4.3 Grade 4

Subjects must discontinue their ARV regimen. The core team should be consulted.

In the event that Grade 2, 3, or 4 rash fails to resolve; increases in severity; is associated with systemic (fever, malaise, nausea) or allergic (e.g., urticaria) symptoms or Grade 3 or 4 LFT elevations; or is associated with exfoliative dermatitis or mucous membrane involvement or erythema, multiforme or suspected Stevens-Johnson syndrome, or necrosis requiring surgery, subjects’ regimen should be discontinued until symptom resolution. The core team must be consulted.

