# 7.0 CLINICAL MANAGEMENT ISSUES

Criteria for subject management, dose interruptions, modifications, and discontinuation or changes in study drug treatment will be mandated only for toxicities attributable to RAL. Toxicities due to FTC/TDF should be managed according to standard clinical practice, with the exception of sections 7.9 and 7.10, with the goal of maintaining continuous therapy, if possible. If any individual study drug must be interrupted or discontinued due to toxicity, then the entire regimen also must be interrupted or discontinued.

The grading system for drug toxicities is located in the Division of AIDS Table for Grading the Severity of Adult and Pediatric Adverse Events (DAIDS AE Grading Table), Version 1.0, December 2004, located at the DAIDS RCC Web Site: http://rcc.tech-res.com/tox_tables.htm.

NOTE: The core team must be notified by e-mail regarding toxicities that result in a change in regimen or discontinuation ([[contact]](mailto:[contact])). Team notification regarding toxicity is especially important during the intensive viral sampling phase in the first 2 weeks of treatment. The protocol does not allow drug substitution for toxicity management.

NOTE: Subjects with HIV/HBV co-infection may experience exacerbation of hepatitis B if FTC/TDF is discontinued.  If discontinuation of FTC/TDF is required, liver function should be monitored closely with both clinical and laboratory follow-up.

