## 7.2 Grade 3 Toxicity

If the investigator has compelling evidence that the AE has NOT been caused by RAL, dosing may continue. Subjects who develop possible RAL-related Grade 3 AEs or toxicities, except as defined in the section 7.0, should have their regimen stopped and the A5248 core team must be consulted. The subject should be reevaluated closely until the AE returns to Grade ≤ 2, at which time their regimen may be reintroduced at the discretion of the investigator or according to standard practice.

If the same Grade 3 AE recurs within 4 weeks, the regimen must be permanently discontinued. If the same Grade 3 AE recurs after 4 weeks but is not thought to be related to RAL, the management scheme outlined above may be repeated.

Subjects experiencing Grade 3 AEs requiring permanent discontinuation of the regimen should be followed closely for resolution of the AE to grade ≤ 2 and the core team must be consulted.

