## 7.3 Grade 4 Toxicity

Subjects who develop a Grade 4 symptomatic AE or toxicity thought to be related to RAL will have their regimen discontinued. If the investigator has compelling evidence that the AE has NOT been caused by RAL, dosing may resume when the AE has resolved to grade ≤ 2.

Subjects experiencing Grade 4 AEs requiring permanent discontinuation of RAL should be followed closely until resolution of the AE to Grade ≤ 2 and the core team must be consulted.

Subjects with Grade 4 asymptomatic laboratory abnormalities in lipids or creatine kinase (CK) may continue RAL.

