## 7.7 AST/ALT Elevations

7.7.1 Grade ≤ 3

The regimen may be continued for asymptomatic, isolated Grade ≤ 3 AST or ALT elevations at the discretion of the site investigator. Careful assessments should be done to rule out the use of alcohol, non-RAL-related drug toxicity, or viral hepatitis as the cause of the Grade 3 elevation.

For symptomatic Grade 3 elevations of AST or ALT, the ARV regimen should be held until toxicity returns to Grade ≤ 2. If symptomatic Grade 3 elevation recurs on rechallenge, the regimen should be discontinued and the core team must be consulted.

7.7.2 Grade 4

The regimen should be held for confirmed asymptomatic AST or ALT Grade 4 elevations until the toxicity returns to Grade ≤ 2. If Grade ≥ 3 elevation in AST or ALT recurs on rechallenge, the ARV regimen should be permanently discontinued and the core team consulted.

Any symptomatic Grade 4 ALT or AST elevation should lead to permanent discontinuation of the ARV regimen if it is suspected to be due to the ARVs. The core team must be consulted.

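### Section 7.4 puts severe skin reactions under the same symptom-limited stop as lesser rash triggers, and for Grade 2 or 3 rash nothing specifically bars rechallenge with the suspected drug

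*Protocol*

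**What the plan says.** The last paragraph of protocol section 7.4 lists circumstances in which a rash of Grade 2, 3 or 4 requires a stop. Some are modest: persistence, worsening, systemic symptoms such as malaise, or allergic symptoms such as urticaria. One is a Grade 3 or 4 LFT elevation. The rest are severe: "exfoliative dermatitis or mucous membrane involvement or erythema, multiforme or suspected Stevens-Johnson syndrome, or necrosis requiring surgery". For all of them, the "regimen should be discontinued until symptom resolution. The core team must be consulted".

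Other sections bear on what happens next:

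- Section 7.0 says that management criteria "will be mandated only for toxicities attributable to RAL". If one drug is stopped for toxicity, "then the entire regimen also must be interrupted or discontinued". It adds: "The protocol does not allow drug substitution for toxicity management".
- Section 7.2, for a possibly RAL-related Grade 3 event, has the regimen stopped until the event is Grade 2 or lower, "at which time their regimen may be reintroduced at the discretion of the investigator or according to standard practice".
- Section 7.3, for Grade 4 events, says: "If the investigator has compelling evidence that the AE has NOT been caused by RAL, dosing may resume when the AE has resolved".
- Section 7.7.2 says that a Grade 4 rise in ALT or AST with symptoms "should lead to permanent discontinuation of the ARV regimen if it is suspected to be due to the ARVs".
- Section 8.1 lists grounds for permanent discontinuation. Its drug-related toxicity item points to 7.1 to 7.3 only. A separate item covers clinical reasons that the physician considers life threatening.

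**The concern.** A stop that ends when symptoms clear suits a rash that itches or lingers. After a suspected Stevens-Johnson syndrome or a similar reaction, the deciding question is whether a study drug caused it, and the paragraph does not ask that. A site that follows the text literally could regard the stop as over once the skin has healed. Because the drugs are stopped together and none may be replaced, resuming the regimen would include the suspected drug. What is at stake is the safety of an individual subject, more than the trial's inference.

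**Working it through.** No figure in the protocol is in dispute, so the check is mainly a reading of the rules side by side.

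**1. Triggers under one rule.** Lesser: non-resolution, worsening, systemic symptoms, allergic symptoms (4). Laboratory: Grade 3 or 4 LFT elevation (1). Severe skin reactions: exfoliative dermatitis, mucosal involvement, erythema multiforme, suspected Stevens-Johnson syndrome, necrosis needing surgery (5). Total 4 + 1 + 5 = 10, all with the same end to the stop.

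**2. What governs the end of the stop, by grade.**

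- Grade 2 rash with a severe feature: 7.1 and 7.4.1 let RAL continue, so the closing paragraph is the only specific stop. It ends on symptoms, with no causality condition.
- Grade 3 rash with a severe feature: 7.4.2 stops the regimen if the rash is thought RAL-related but gives no end. Section 7.2 allows reintroduction at Grade 2 or lower even when RAL is a possible cause. It makes the stop permanent if the same Grade 3 event recurs within 4 weeks, which is after re-exposure has taken place.
- Grade 4 rash: 7.4.3 stops the regimen whatever the cause and gives no end. Section 7.3 offers resumption only with compelling evidence of a non-RAL cause, whereas the closing paragraph ties the end to symptoms.
- Rash with symptomatic Grade 4 ALT/AST elevation suspected to be due to the ARVs: 7.7.2 calls for a permanent stop, and the closing paragraph for a temporary one. No order of precedence is given.

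**3. How the protocol words other stops.** It writes a permanent stop where it intends one: recurrent Grade 3 events in 7.2, the Grade 4 rules in 7.7.2, and confirmed low creatinine clearance in 7.9. Sections 7.5, 7.6 and 7.7 each say what to do if the toxicity returns when treatment is resumed. Section 7.4 contains neither kind of rule.

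**4. Reach of the safeguards.** Core team consultation is mandatory in the closing paragraph, but nothing says that it must come before a restart or what it must settle. Section 7.3 protects only at Grade 4 and asks only about RAL. The life-threatening item in 8.1 depends on judgement, and its drug-toxicity item does not cite 7.4.

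**5. Size.** The protocol gives no rate, so every input here except n = 34 is an assumption. With per-subject risk p of a severe reaction, the chance of at least one is 1 − (1 − p)^34:

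- p = 0.1%: 1 − 0.999^34 = 3.3%
- p = 1%: 1 − 0.99^34 = 28.9%

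With a share c that is drug-related and a share r of those restarted, the chance of at least one re-exposure is 1 − (1 − p·c·r)^34:

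- p = 0.1%, c = 0.5, r = 0.1: 0.17%
- p = 1%, c = 0.5, r = 0.1: 1.7%
- p = 1%, c = 0.5, r = 0.5: 8.2%

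The spread of nearly fifty-fold shows how little these figures can carry beyond indicating a rare event.

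**6. Effect on the analyses.** Section 9.4 drops RNA values obtained after treatment interruptions, while 9.6.1 ties its interruption exclusion to days 0 to 14. A later interruption is therefore not clearly excluded from the fit through day 56. With very few subjects concerned, the first-phase estimate is essentially untouched. A permanent stop does count in the discontinuation endpoint (9.2.2.4), and such subjects stay in the ITT suppression and CD4 analyses (9.6.2.3 and 9.6.2.5).

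**The case against.** The best defence is that the phrase sets a minimum hold and grants no permission to restart. Sections 7.2 and 7.3 say openly when dosing may resume; the 7.4 paragraph does not. It also speaks of discontinuing, where 7.5 to 7.7 speak of holding. On that reading a site can obey 7.4 together with 7.3 or 7.7.2, and the core team is involved in any case. The reading is possible but strained, given how plainly the protocol marks permanent stops elsewhere. It does mean that the clashes with 7.3 and 7.7.2 are tensions and not outright contradictions.

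A second point is that grades come from the DAIDS table, which is not reproduced. If that table places these features at Grade 4, then 7.3 and 7.4.3 already govern most RAL-related cases and the gap shrinks. That cannot be settled here, but the 7.4 sentence itself contemplates these features with Grade 2 or 3 rash.

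Third, rarity and oversight count for something. The protocol's background reports no serious adverse events in the treatment-naïve RAL trial, and a committee that includes the DAIDS medical officer reviews toxicity monthly. This limits the expected harm but does not correct the rule.

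A reader might infer that nothing in the protocol bars rechallenge, or that restart turns on symptoms alone. The documents do not support that: 7.3 ties Grade 4 resumption to a non-RAL cause, and 8.1 permits a permanent stop for life-threatening reasons. Nor is any restart ordered.

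**Conclusion.** The point holds in a limited form. One symptom-based stop covers severe and lesser triggers alike. For Grade 2 or 3 rash with severe features, no text specifically prevents re-exposure, and protection comes from consultation and judgement. For RAL-related Grade 4 rash, and for rash with symptomatic Grade 4 ALT/AST elevation suspected to be due to the ARVs, the wording pulls against 7.3 and 7.7.2. There is no fault for Grade 3 rash without severe features, where 7.2 deliberately allows reintroduction.

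The size cannot be derived from the protocol. The event is likely rare in 34 subjects, and the percentages above are illustrations under assumed rates. It would also go too far to say that no result is affected, since the few subjects concerned enter the discontinuation endpoint and the ITT analyses. The conclusion assumes that sites read the closing paragraph as a temporary stop and that the grading table does not already place every such reaction at Grade 4. The possible harm is serious and cheap to prevent, so the text should be changed.

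**What to change.** - Take the five severe reactions out of the sentence. For them, require permanent discontinuation of the regimen with no rechallenge, unless there is compelling evidence that the study drugs were not the cause and the core team agrees before any restart.
- For mucosal involvement, apply this when it accompanies the rash as a suspected drug reaction. Let the core team judge mild or clearly unrelated lesions, so that a trivial lesion does not end treatment by default.
- State that 7.3 governs RAL-related Grade 4 rash, and that the stricter of 7.4 and 7.7 applies when LFTs are elevated.
- Keep the hold until symptoms resolve, with consultation, for the lesser triggers.
- Add 7.4 and 7.7 to the cross-reference in 8.1. Because the new rule asks about all study drugs, 7.4 should also join 7.9 and 7.10 as an exception in 7.0, which otherwise leaves FTC/TDF toxicity to standard practice.

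The cost is a wording change, with no added visit, test or sample. The downside is that a rare subject can no longer restart the study regimen. That subject is followed off drug under 6.2.3 and counts as a permanent discontinuation.

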## 7.5 Nausea/Vomiting

Nausea/vomiting may be treated symptomatically with oral antiemetics or antiemetic suppositories. For Grade ≥ 3 nausea and vomiting thought secondary to RAL that fails to improve on antiemetics to Grade ≤ 2, the regimen may be held until Grade ≤ 2. If Grade ≥ 3 nausea and vomiting recurs with reinstitution of RAL or persists beyond 14 days despite symptomatic management, then their regimen may be discontinued at the discretion of the investigator and in consultation with the core team.

## 7.6 Diarrhea

Symptomatic treatment of any grade diarrhea with oral antidiarrheal drugs is permitted once infectious causes of diarrhea have been ruled out by the site investigator. If Grade ≥ 3 diarrhea thought to be related to RAL persists despite symptomatic management, then the regimen should be held until Grade ≤ 2. If Grade ≥ 3 diarrhea recurs with reinstitution of RAL or persists beyond 14 days despite symptomatic management, then the regimen should be discontinued and the core team consulted.

## 7.7 AST/ALT Elevations

7.7.1 Grade ≤ 3

The regimen may be continued for asymptomatic, isolated Grade ≤ 3 AST or ALT elevations at the discretion of the site investigator. Careful assessments should be done to rule out the use of alcohol, non-RAL-related drug toxicity, or viral hepatitis as the cause of the Grade 3 elevation.

For symptomatic Grade 3 elevations of AST or ALT, the ARV regimen should be held until toxicity returns to Grade ≤ 2. If symptomatic Grade 3 elevation recurs on rechallenge, the regimen should be discontinued and the core team must be consulted.

7.7.2 Grade 4

The regimen should be held for confirmed asymptomatic AST or ALT Grade 4 elevations until the toxicity returns to Grade ≤ 2. If Grade ≥ 3 elevation in AST or ALT recurs on rechallenge, the ARV regimen should be permanently discontinued and the core team consulted.

Any symptomatic Grade 4 ALT or AST elevation should lead to permanent discontinuation of the ARV regimen if it is suspected to be due to the ARVs. The core team must be consulted.

## 7.8 Lactic Acidosis/Symptomatic Hyperlactatemia

Symptomatic hyperlactatemia will be defined as new, otherwise unexplained, and persistent occurrence for >2 weeks of one or more of the following:

- nausea and vomiting
- abdominal pain or gastric discomfort
- abdominal distention
- increased LFTs
- unexplained fatigue
- dyspnea
- motor weakness

plus a confirmed lactate level >2 x ULN.

If the lactate value is >2 x ULN, obtain a confirmatory lactate value as soon as possible, preferably within 1 week, and consult the core team. Study medication should be discontinued immediately if the confirmatory value remains >2 x ULN or if the site is unable to obtain a confirmatory value within1 week. Determine lactate levels every 4 weeks until the lactate value returns to normal.

Management of symptomatic lactate value <2 x ULN will proceed at the discretion of the investigator. However, any modification of a subject's ARV regimen should be made in consultation with the core team. Since some of the symptoms of hyperlactatemia are vague and may be present in many subjects (e.g., fatigue), repeated lactate determinations are advised.

NOTE: See the ACTG Web site for guidelines for the collection of lactate specimens ([**https://www.actgnetwork.org/members/download/other/Metabolic/VenousLactateSOP.doc**](https://www.actgnetwork.org/members/download/other/Metabolic/VenousLactateSOP.doc)).

## 7.9 Decreased Creatinine Clearance

If the calculated CrCl is <50mL/min*, it should be confirmed within 1 week. If the calculated CrCl remains <50ml/min, the regimen must be permanently discontinued and the core team notified.

*Calculate a CrCl from the serum creatinine concentration in mg/dL using the Cockcroft and Gault equation. (Refer to section 4.1.4)

## 7.10 Skin Hyperpigmentation

The development of skin hyperpigmentation, if assessed as being related to FTC, can be followed without modification of therapy, at the discretion of the investigator.

## 7.11 Headache

Analgesics, antimigraine drugs, muscle relaxants, and other symptomatic treatment should be used at the discretion of the investigator, and the subjects may continue on RAL. The subject should be advised to contact the physician immediately if there is any worsening of the headache.

If the headache is considered to be most likely due to concomitant illness or drug, standard management, including discontinuation of the likely causative agent, should be undertaken. If no other causative factor is found after clinical evaluation, the subject should be treated symptomatically.

If the headache is thought to be related to RAL, the subject should be managed at the discretion of the investigator. If the ARV regimen is discontinued, the core team must be consulted.

## Pregnancy

Subjects who become pregnant after study entry must discontinue study medication immediately. Subjects will come in for a premature discontinuation of study medications visit within 14 days after stopping all drugs. They will continue to be followed on study/off study medication, as per the section 6.1, but do not require blood draws for PK studies and stored plasma/PBMCs or completion of self-reported adherence assessment. The core team must be notified of any pregnancies that occur for subjects on study ([[contact]](mailto:[contact])).

Pregnancies that occur on study should be reported to The Antiretroviral Pregnancy Registry. More information is available at [www.apregistry.com](http://www.apregistry.com/). [contact]; [contact].

Intrapartum complications and/or pregnancy outcome will be recorded on the CRFs up to week 72 and also should be reported to The Antiretroviral Pregnancy Registry. After week 72, intrapartum complications and/or pregnancy outcome will be reported only to The Antiretroviral Pregnancy Registry.

# 8.0 CRITERIA FOR DISCONTINUATION

## 8.1 Permanent Treatment Discontinuation

- Drug-related toxicity (see section 7.1-7.3 Toxicity).
- Requirement for prohibited concomitant medications (refer to section 5.4).
- Completion of treatment as defined in the protocol.
- Request by subject to terminate treatment.
- Clinical reasons thought life threatening by the physician, even if not addressed in the toxicity section of the protocol.
- Pregnancy or breast-feeding.

## 8.2 Premature Study Discontinuation

- Subject misses 3 consecutive clinic visits.
- Between weeks 12 and 72, subject misses more than 25% of study medications (since the last visit, self-report).
- Request by the subject to withdraw.
- Request of the primary care provider if s/he thinks the study is no longer in the best interest of the subject.
- Subject judged by the investigator to be at significant risk of failing to comply with the provisions of the protocol as to cause harm to self or seriously interfere with the validity of the study results.
- A defined study endpoint reached (virologic failure as defined in section 3.0)*.*
- At the discretion of the ACTG, IRB, Food and Drug Administration (FDA), Office for Human Research Protections (OHRP), NIAID, investigator, or pharmaceutical supporter.

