# 3.0 STUDY DESIGN

A5248 is a prospective, open-label, multicenter, 72-week pilot study designed to estimate the first-phase viral decay rate in subjects receiving RAL and FTC/TDF. HIV-infected ARV-naïve subjects (defined as no previous ARV treatment at any time prior to entry) with plasma HIV-1 RNA levels ≥10,000 and ≤ 300,000 copies/mL obtained within 42 days prior to study entry will be enrolled. Subjects will be ineligible if the screening genotype shows the existence of major NRTI, NNRTI, or PI resistance mutations. There will be no CD4+ T-cell count restriction.

Thirty-four subjects will each be followed for 72 weeks. It is anticipated that the 34 subjects will be accrued within 8 months of the study opening to accrual. Subjects will have plasma HIV-1 RNA and CD4+ T-cell count measurements at pre-entry and entry. The geometric and arithmetic means, respectively, of these measurements will be used to establish their baseline values.

Real-time genotyping for drug resistance will be performed at screening, if not already available, and at the time of virologic failure. The study will provide all the resistance assays. Subjects will also undergo frequent routine safety monitoring, including hematology, chemistry evaluations, and urinalyses.

Virologic failure will be defined as a confirmed plasma HIV-1 RNA level ≥ 1000 copies/mL at or after 16 weeks and before 24 weeks, or ≥ 200 copies/mL at or after 24 weeks.

When a subject is suspected to have virologic failure, a confirmatory HIV-1 RNA and a plasma sample for real-time plasma HIV-1 RNA genotype will be collected within 14 days. The specimen collected for genotype at that visit will be sent for resistance testing once virologic failure has been confirmed. It is recommended that subjects continue their regimen while genotypic resistance testing is being performed.

Adherence to all study drugs will be monitored by self-report as per the Schedule of Events. All subjects should be provided adherence reinforcement throughout the study, according to local standard practice. Subjects with poor adherence will be provided counseling by the site. Trough plasma samples will be collected from all subjects for PK analyses (see section 10.0).

Subjects who modify the study regimen or miss doses are expected to stay on study and will be followed; however, in some situations, subjects will be replaced (see section 9.1).

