6.2.3 Discontinuation Evaluations

Evaluations for Registered Subjects Who Do Not Start Study Treatment

Subjects who do not begin study treatment should have screening, pre-entry, and entry forms completed and keyed. Beyond the entry visit, no further evaluations are required.

Premature Discontinuation of Study Medications Evaluations

Subjects who discontinue the study medications before the end of the study will come in for a premature discontinuation of study medications visit within 14 days after stopping study drugs. They will be encouraged to continue to attend all study visits for the duration of the study but do not require blood draws for PK studies and stored plasma/PBMCs or completion of self-reported adherence assessment for the duration of the study.

Final Study Evaluations/Premature Study Discontinuation Evaluations

All subjects who complete the study (at week 72) or prematurely discontinue participation in the study should report to the clinic to have the final visit evaluations performed (section 6.1).

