# 9.0 STATISTICAL CONSIDERATIONS

## 9.1 General Design Issues

This is a prospective, single-arm, 72-week pilot study to estimate the first-phase viral decay constant (d1) in treatment-naïve subjects initiating a three-drug regimen consisting of the HIV-1 integrase inhibitor RAL and NRTI combination FTC/TDF.

In general, analyses that address mechanisms of pathobiology will be conducted on subjects as treated (AT), and analyses of markers for clinical outcome will be ITT. The accrual target of 34 subjects is expected to yield plasma HIV-1 RNA data from 30 subjects for model-fitting, and thus provide a 95% CI around the estimated d1 of no wider than ±0.07, assuming the population mean and standard deviation of d1 for the study regimen are 0.80 and 0.20, respectively. Under these assumptions, with usable data from 30 subjects, there is 98% probability that the CI around the estimated d1 will exclude the value 0.65.

Subjects who modify the study regimen or miss doses are expected to stay on study and be followed; however, they will be replaced as follows: If the subject changes the regimen or misses any dose from day 0 through 14, an additional subject will be accrued. For every three subjects who change regimen or miss 2 or more doses from day 15 through 56, an additional subject will be accrued. (Although subjects dropping out before day 57 will be replaced in this way, the buffer of 4 additional subjects [Section 9.4] is retained to allow for missing results on obtained samples.) Such subjects will be excluded from AT analyses and included in ITT analyses. (See Section 9.6 for details.) From day 57 and thereafter, subjects altering the treatment regimen or missing doses will not be replaced; those who alter the regimen or miss more than 7 cumulative days of doses will be excluded from AT and included in ITT analyses.

The primary objective will be analyzed when plasma HIV-1 RNA results through day 28 are available (as quantified using the standard assay). Specifically, when the last subject to enroll has reached day 21, sites will be asked to send those batched plasma HIV-1 RNA samples that are intended for standard assay to the assay lab (Johns Hopkins University). When results for these samples and when the real-time results for the day 28 and 56 samples are available, analysis to estimate first and second phase viral decay rates will begin.

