9.6.2.3 To determine the proportion of subjects with plasma HIV-1 RNA below the limit of detection, <50 copies/mL, 24, 48, and 72 weeks after initiation of RAL and FTC/TDF.

The primary analysis will be an ITT analysis, wherein (1) if the study regimen (RAL and/or FTC/TDF) is modified or discontinued, the subject is retained in analyses, and (2) if a subject is lost to follow-up, the last observation is carried forward for subsequent time points. The proportion of subjects with plasma HIV-1 RNA <50 copies/mL at weeks 24, 48, and 72 will be reported along with the exact binomial 95% CI.

A secondary AT analysis will include only those subjects on the study regimen at the time of the evaluation.

9.6.2.4 To evaluate the safety and tolerability of the treatment with RAL and FTC/TDF.

Among subjects taking one or more doses of study drug, the proportion exhibiting each category of events will be reported, along with exact binomial 95% CI. Incidence rates, i.e., numbers of events per person-months of follow-up, will also be reported.

9.6.2.5 To evaluate changes in CD4+ T-cell counts 24, 48, and 72 weeks after initiation of RAL and FTC/TDF.

For the primary analysis, using the ITT approach described in 9.6.2.3, changes in CD4+ T-cell counts at weeks 24, 48, and 72 will be summarized descriptively via mean, SD, median, and quartiles. A secondary AT analysis may also be performed.

9.6.2.6 To investigate the occurrence of RAL and FTC/TDF-resistance mutations at virologic failure using very sensitive resistance assay techniques

Among subjects who took any dose of study drug, for each failing subject, the list of resistance mutations present at failure, if any, will be displayed. Of failing subjects, the proportion with specific mutations (ones occurring frequently among A5248 failures, ones known to be associated with RAL resistance) will be reported along with exact binomial 95% CIs.

9.6.2.7 To evaluate the relationship of RAL and FTC/TDF PK parameters with virologic and immunologic responses, including day 7 plasma HIV-1 RNA change from baseline and the magnitude and slope of changes in CD4+ T-cell counts over the first 14 days of study drug.

RAL, TDF, and FTC PK trough averages at steady state will be estimated.

9.6.2.8 To evaluate adherence by self-report in treatment-naïve subjects receiving RAL and FTC/TDF.

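### Section 8.2 takes subjects who miss more than 25% of doses after week 12 off study, while 3.0 and 9.1 keep them for the ITT analyses; the rules need reconciling and follow-up should continue (secondary endpoints only)

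*Protocol*

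**What the plan says.** Section 8.2 gives the criteria for leaving the study early. One of them is: "Between weeks 12 and 72, subject misses more than 25% of study medications (since the last visit, self-report". No exception is written. Grounds for stopping treatment stand apart, in 8.1.

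Other sections keep such subjects in follow-up:

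- Section 3.0: "Subjects who modify the study regimen or miss doses are expected to stay on study and will be followed". Section 9.1 repeats this and adds that, from day 57, "those who alter the regimen or miss more than 7 cumulative days of doses will be excluded from AT and included in ITT analyses".
- Section 9.6.2.3, on the ITT analysis of HIV-1 RNA below 50 copies/mL: "if the study regimen (RAL and/or FTC/TDF) is modified or discontinued, the subject is retained in analyses". Sections 9.6.2.5 (CD4+ change) and 9.6.2.10 (single-copy results, weeks 24 to 72) use the same ITT approach.
- Section 6.2.3, on subjects who stop study medication early: "They will be encouraged to continue to attend all study visits for the duration of the study". The adherence self-report is waived for them.
- Section 7.12, on pregnant subjects: "They will continue to be followed on study/off study medication, as per the section 6.1". The same waiver applies.

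The protocol also directs holds that may be followed by restarting, for example in 7.7.2: "The regimen should be held for confirmed asymptomatic AST or ALT Grade 4 elevations until the toxicity returns to Grade ≤ 2". Section 7.2 is similar for Grade 3 events possibly related to raltegravir. Neither section limits the length of the hold. Section 6.3.5 records protocol-mandated interruptions together with subject-initiated ones.

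**The concern.** Read literally, 8.2 and 9.1 give opposite instructions for the same subject. A site that follows 8.2 ends participation; a site that follows 3.0 and 9.1 continues the visits. Nothing separates a dose missed through poor adherence from one withheld on the protocol's own direction.

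At stake are the data behind the secondary ITT analyses. A subject who leaves the study has one final visit (6.2.3) and nothing is scheduled after it. HIV-1 RNA, CD4+ count and safety laboratory data then end for subjects selected because they had trouble with the regimen. The expedited adverse event reporting period in 11.4 also ends at discontinuation from the study. Samples that were not drawn cannot be recovered at analysis.

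**Working it through.** **1. The protocol's main design figure, to see whether it is touched.** Inputs (9.1, 9.4): n = 30 usable subjects, mean d1 0.80, SD 0.20, reference value 0.65.

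- Standard error = 0.20/√30 = 0.0365.
- 95% CI half-width = 1.96 × 0.0365 = 0.072 (0.075 with the t quantile on 29 df). The protocol states 0.07.
- Probability that the CI lies above 0.65 = Φ(0.15/0.0365 − 1.96) = Φ(2.15) = 98.4%, or 97.8% by the noncentral t. The protocol states 98%.

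The figure reproduces. The estimate of d1 uses HIV-1 RNA through day 56 (9.2.1), and the 8.2 criterion starts at week 12 (day 84). The primary endpoint, sample size and power are therefore not affected.

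**2. When is the 8.2 criterion met?** Visit weeks from the Schedule of Events: 12, 16, 20, 24, 36, 48, 60, 72. Section 7.0 requires the whole regimen to be interrupted when one drug is interrupted for toxicity, so days off drug is the right unit for a hold.

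- Weeks 12 to 24: interval 28 days; 25% × 28 = 7 days. Eight days missed gives 8/28 = 28.6%.
- Weeks 24 to 72: interval 84 days; 25% × 84 = 21 days. Twenty-two days missed gives 22/84 = 26.2%.
- These are nominal. Each of these visits has a ±7-day window, so a 28-day interval can run from 14 to 42 days. At 42 days, 8 missed days is 8/42 = 19% and does not meet the criterion.

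**3. The rules side by side.**

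- *On treatment, misses 8 days between weeks 16 and 20.* Section 8.2: leaves the study. Section 9.1: more than 7 cumulative days, so out of as-treated, kept in ITT. Section 3.0: stays on study. Direct conflict.
- *Toxicity hold longer than 7 days in a 4-week interval, or 21 in a 12-week interval.* Section 8.2 has no exception and 6.3.5 groups such holds with other interruptions, so the criterion is met as written. Sections 3.0, 9.1 and 9.6.2.3 keep the subject. Conflict.
- *Shorter hold.* The criterion is not met. No conflict.
- *Permanently stopped, or pregnant.* Removal follows only if missing medication includes medication that has been stopped. Sections 6.2.3 and 7.12 provide for follow-up and waive the self-report on which 8.2 depends. Ambiguous.

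**4. Possible size for the proportion below 50 copies/mL.** The protocol gives no expected number of affected subjects, so this is an illustration on assumed counts. Each subject is 1/34 = 2.9 percentage points. Assume 30 of 34 are counted as suppressed, with every removed subject carried forward as suppressed: 30/34 = 88.2% (exact 95% CI 72.5 to 96.7). If the removed subjects were in fact unsuppressed at the later visit:

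- 1 removed: 29/34 = 85.3%
- 3 removed: 27/34 = 79.4% (62.1 to 91.3)
- 5 removed: 25/34 = 73.5% (55.6 to 87.1)

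This is the unfavourable extreme. Section 9.6.2.3 prescribes carrying the last observation forward for loss to follow-up and does not say whether removal under 8.2 counts as that. The value carried could be a suppressed one from before the interruption. It could also be the final-visit value, since that visit includes HIV-1 RNA, and then the error can go either way.

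**The case against.** Several stronger readings are tempting, and the documents do not support them.

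- *That 8.2 expels everyone who stops treatment or becomes pregnant.* A reader might infer this because they take no doses. But 8.1 separates stopping treatment from leaving the study, the 8.2 trigger is self-reported, and 6.2.3 and 7.12 waive that report while specifically providing for continued follow-up. A drug stopped for good is not naturally a missed dose. What remains is that the text does not exclude these subjects expressly, so sites may differ.
- *That the ITT analyses would have no data on removed subjects.* Everything up to removal exists, and the final visit includes HIV-1 RNA, CD4+ count, chemistry and liver tests. Only later data are lost.
- *That a stated share of the ITT data is lost.* The protocol gives no number of subjects who would meet the criterion, and removal can fall at any visit up to week 72.
- *That safety follow-up stops altogether.* Sections 7.2 and 7.3 separately require close follow-up until Grade 2 or lower after permanent discontinuation for toxicity, and pregnancies are also reported to the pregnancy registry. The effect on the reporting period in 11.4 is real but narrower.
- *That the criterion should simply be deleted.* Raltegravir is supplied by the study and 8.1 has no adherence threshold, so deletion would settle a discontinuation question that belongs to the sponsor.

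It is also fair to say that this is a 34-subject single-arm pilot whose primary estimate is complete before the criterion applies. That lowers the severity. It does not remove the conflict for subjects who miss doses or are on longer holds.

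**Conclusion.** The point holds in a limited form. For subjects on treatment who miss doses, and for those on longer toxicity holds, 8.2 contradicts 3.0, 9.1 and 9.6.2.3. The threshold is more than 7 days in a 4-week interval or more than 21 days in a 12-week interval, at nominal spacing. For subjects who have permanently stopped or are pregnant, 8.2 is unclear.

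The consequence is selective loss of data after the final visit for the ITT analyses at weeks 24, 48 and 72 and for the single-copy analysis over weeks 24 to 72. Each affected subject moves a proportion by at most 2.9 percentage points. The total depends on how many are affected, which the protocol does not say, and on whether last-observation-carried-forward applies to them. The primary objective is untouched. This should be fixed, for the sake of the secondary endpoints only.

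**What to change.** Reconcile 8.2 with 3.0, 6.2.3, 7.12, 9.1 and 9.6.2.3 in an amendment:

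- State whether the 25% criterion applies to protocol-directed holds and to subjects who have stopped treatment.
- State that, whatever is decided about study drug, subjects who meet the criterion are asked to continue the visits already scheduled, to week 72, for HIV-1 RNA, CD4+ count and safety laboratory tests. The ITT analyses then have the data they assume.

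Which treatment or discontinuation rule applies is for the sponsor to decide; this change concerns follow-up and data collection. The cost is a short clarification and a few visits, already in the schedule, for subjects who would otherwise have left.
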